## Abstract

**Background:**

Research suggests that altered eating and the pursuit of thinness in anorexia nervosa (AN) are, in part, a consequence of aberrant reward circuitry. The neural circuits involved in reward processing and compulsivity overlap significantly, and this has been suggested as a transdiagnostic factor underpinning obsessive compulsive disorder, addictions and eating disorders. The nucleus accumbens (NAcc) is central to both reward processing and compulsivity. In previous studies, deep-brain stimulation (DBS) to the NAcc has been shown to result in neural and symptomatic improvement in both obsessive compulsive disorder and addictions. Moreover, in rats, DBS to the NAcc medial shell increases food intake. We hypothesise that this treatment may be of benefit in severe and enduring anorexia nervosa (SE-AN), but first, feasibility and ethical standards need to be established. The aims of this study are as follows: (1) to provide feasibility and preliminary efficacy data on DBS to the NAcc as a treatment for SE-AN; (2) to assess any subsequent neural changes and (3) to develop a neuroethical gold standard to guide applications of this treatment.

**Method:**

This is a longitudinal study of six individuals with SE-AN of >7 years. It includes an integrated neuroethical sub-study. DBS will be applied to the NAcc and we will track the mechanisms underpinning AN using magnetoelectroencephalography, neuropsychological and behavioural measures. Serial measures will be taken on each intensively studied patient, pre- and post-DBS system insertion. This will allow elucidation of the processes involved in symptomatic change over a 15-month period, which includes a double-blind crossover phase of stimulator on/off.

**Discussion:**

Novel, empirical treatments for SE-AN are urgently required due to high morbidity and mortality costs. If feasible and effective, DBS to the NAcc could be game-changing in the management of this condition. A neuroethical gold standard is crucial to optimally underpin such treatment development.

**Clinical Trial Registration:**

The study is ongoing and registered with www.ClinicalTrials.gov, https://clinicaltrials.gov/ct2/show/NCT01924598, 22 July, 2013. It has full ethical and HRA approval (Project ID 128658).

## Introduction

Anorexia nervosa (AN) is one of the most challenging psychiatric disorders to treat, and its mortality rate is the highest amongst the psychiatric disorders (1, 2). It becomes severe and enduring anorexia nervosa (SE-AN) in at least a third of cases. There remains a grave paucity of evidence-based psychological therapies for AN (3–5), and there are few psychopharmacological treatments of benefit (6–8). The lack of effective treatments for SE-AN leads to huge morbidity costs to individuals and health-care services (9), so the development of novel, empirically-based and effective treatments is of major importance. This study investigates whether deep-brain stimulation (DBS) of the ventral anterior limb of the internal capsule (ALIC) within the nucleus accumbens (NAcc) is acceptable, feasible and helpful for adults with SE-AN.

DBS is a reversible, adjustable, non-destructive intervention using a surgically implanted medical device, which delivers carefully controlled electrical pulses to precisely targeted brain areas. While the exact mechanisms of action remain unclear, it has been suggested that DBS works by rebalancing resting-state networks (RSNs) in the brain. Neuroimaging studies have demonstrated that RSNs are abnormal in AN (10–12). In this study, we will use magnetoencephalography (MEG) to monitor post-operative changes in neural activity. Recordings will be made both in the resting state and also during a food reward task in which participants are asked how much they want high- vs low-calorie food stimuli. MEG scanning is a real-time measure of neural responses, which we have previously used to demonstrate attentional bias to food cues in a currently ill population (13).

DBS has been widely used, particularly for Parkinson’s disease, for over 30 years. Increasingly over the last decade, DBS has been applied to the treatment of psychiatric disorders including treatment-resistant depression (14–17), obsessive compulsive disorder (OCD) (18, 19) and addictions (20). The US Food and Drug Administration approved a humanitarian device exemption for DBS in the treatment of severe OCD in 2009. This resulted from a review of data from 26 patients with severe treatment-resistant OCD who underwent DBS to the ALIC/ventral striatum (VS). On average, after 12 months of therapy, there was a 40% reduction in patients’ OCD symptoms (21).

Two lines of evidence indicate that DBS might be effective in SE-AN. Firstly, OCD and AN are highly co-morbid, with both disorders showing a high degree of compulsivity (22–24). The second arises from case reports and series. A patient with severe OCD also found improvement in co-morbid anorexia following DBS (25). Further case reports and case series of DBS for SE-AN (26–28) suggest benefit, although none have included double-blind DBS on–off phases. The largest case series, of 6 patients with SE-AN (29) involved DBS applied to the subcallosal cingulate, a neural target previously used for treatment-resistant depression. Regarding safety, the authors initially reported one serious adverse event (SAE): a seizure 2 weeks post-operatively in the context of AN-related metabolic disturbance, with no permanent sequelae. A further patient had a panic attack intraoperatively, and another had an air embolism, but there were no long-lasting adverse effects of the surgery for either participant. A follow-up paper reported sustained symptomatic improvement and weight restoration in three out of six patients, possibly mediated by improvements in mood regulation (30). A recent single case study has also reported improvement in eating disorder psychopathology and mood in an individual with chronic AN, following DBS to the bed nucleus of the stria terminalis (28).

Individuals with AN experience an aberrant sense of reward from weight loss and self-starvation (9, 31, 32) with neural evidence that reward processing becomes abnormal (33, 34). Energy-dense food is anxiety-provoking and aversive, such that individuals become unable to eat to sustain life (35, 36). The compulsive pursuit of self-starvation in AN represents a major barrier to treatability, rendering contemporary treatments highly aversive and contributing to high dropout and relapse rates (31, 37). If these disturbed reward processes could be characterised and subsequently interrupted at a neural level, it would revolutionise the treatment of AN.

The NAcc, located deep in the VS, is central to reward processing and has been described as a “hedonic hotspot” [38]. In rats, DBS to the medial shell of the NAcc has been shown to increase food intake (39), and activity in this structure is key to experiencing food as rewarding (38). Neuroimaging and experimental studies in AN (31, 32, 37) confirm a dysregulation of reward circuitry: in particular, an abnormal striatal response to food and thinness cues (33, 34, 40). There is also evidence of an increased top-down control over reward circuitry in AN, emanating from the prefrontal cortex (41).

The relentless self-starvation and over-exercising seen in AN have parallels with OCD and addictions with evidence of aberrant reward processing in common with these other pathologies (22, 24, 42–45). There is evidence that compulsivity is a transdiagnostic process common across these disorders (23), mediated at a neural level by corticostriatal thalamic circuits, which incorporates the VA and NAcc (46). Excessive reliance on habit formation in learning has been suggested as the basis of persistent compulsive behaviour in OCD (47) and more recently in AN (9). It has been suggested that restrictive eating and weight loss in AN begin as “action-outcome/goal-directed learning” in which behaviour is associated with a rewarding outcome (44). However, through repetition, reward processing becomes aberrant such that the behaviour no longer relies upon reward reinforcement (stimulus–response learning), and this behaviour becomes highly resistant to change (48). This reduction in goal-directed learning in eating disorders has been demonstrated using a two-step habit formation task (49). This task will also be undertaken by participants in this study to record any changes in compulsive, habitual responding (50).

Given the high mortality and morbidity rates of SE-AN (51), additional risks to patients of surgery and entering this study are small, with a potential cost–benefit analysis that justifies ethical equipoise (52). [name], who performs all the DBS operations, has an excellent personal safety record and has performed thousands of operation on patients with Parkinson’s disease. He has also operated on adults with chronic pain and children with movement disorders. The procedure itself has an overall risk of stroke of less than 1%, a haemorrhage-causing death of 0.01% and a risk of wound infection of 5%. To minimise the risk of surgery, the patients will be medically stable prior to surgery. They must have a normal ECG and electrolytes, be free of severe binging or purging or severe depression/suicidality, both of which pose added background risks. The technique (as performed in Oxford) is very well tolerated and can be done in one stage, supported by two to four nights as an inpatient in the neurosurgical ward. DBS has a one-off cost of approximately £40,000 to implant a rechargeable device with a 10-year lifespan. As the mechanisms, efficacy and optimal DBS target for intervention in AN are yet to be established, it should be regarded as an experimental treatment, with the risk that it will not be effective. However, given the extremely poor outcome in terms of morbidity and mortality for those with SE-AN, it is plausibly an intervention where the benefits may outweigh the risks and costs.

A significant body of research suggests that altered reward processing contributes to the maintenance of SE-AN and that this is influenced by higher cognitive control processes (9). We hypothesise that DBS to the NAcc may ameliorate aberrant reward processing and AN psychopathology.

In this clinical trial, our aims are to examine (1) the safety, acceptability and feasibility of DBS to the ALIC at the NAcc in SE-AN; (2) to map neural mechanisms and symptomatic change following DBS; (3) to explore ethical issues, capacity, consent and patients’ views pre- and post DBS and (4) to explore the longer-term effects of DBS in SE-AN.

## Methods

This is a study of DBS targeting the NAcc in up to six patients with SE-AN, using pre- and post-operative repeated measures. To date, five patients have been enrolled in the study.

The study period is 15 months—see Figure 1 for details of study interventions. There will be pre-operative assessments in month 1, the DBS operation in month 2, followed by the DBS switch-on at the end of month 3. DBS dose will be optimised during months 3–6. During month 10 of the study (6 months after switch-on), there will be two double-blinded 2-week periods of DBS on/off as described by Denys et al. (53). At 15 months (12 months after switch-on), there will be final follow-up tests. This study is a quantitative and qualitative investigation of eating disorder and co-morbid pathology, using MEG to image neural processes, and computerised tasks to assess habit formation. There is also a parallel quantitative and qualitative sub-study of ethical issues involved.

**Figure 1 F1:**
[figure not shown]
Schedule of study procedures.

### Patient Population and Recruitment

#### Inclusion Criteria

Primary diagnosis: AN according to the DSM-V criteria, based on a psychiatric interviewIllness duration of severe AN of >7 yearsDisabling severity with substantial functional impairmentTreatment refractoriness, defined as lack of response to two or more typical modes of treatment, such as inpatient weight restoration, psychotherapy and psychopharmacologySeverely underweight: Body Mass Index (BMI) > 13 < 1621–65 years oldWritten informed consentAble to fully understand the consequences of the procedureEnglish speaking and able to answer the study questions fluentlyHas the mental capacity to provide informed consent to research participation

#### Exclusion Criteria

Unstable physical condition (severe electrolyte disturbances, cardiac failure and other physical conditions due to low weight in which surgery/anaesthesia is contraindicated)Treatable underlying cause of anorexia/underweightParkinson’s disease, dementia, epilepsyHistory of schizophrenia/psychosis, bipolar disorderAlcohol or substance abuse (including benzodiazepines) during the last 6 monthsCurrent severe major depressive or Tic disorderAntisocial or severe Borderline Personality DisorderStandard MRI scan exclusion criteria (pregnancy, pacemaker and metals contraindicated for MRI, except for the DBS implantation and stimulator itself)Currently an involuntary patient

### Patient Selection Process

The study patients will have SE-AN. Individuals fulfilling inclusion and exclusion criteria under the clinical care of specialist eating disorder services will be ranked in the order of suitability according to the below specific criteria:
Degree of severity and intractability of ANHas never had periods of full remissionHas tried existing treatment options without successIntensity of desire to recoverRestrictive AN—without bingeing/purgingAbsence of currently severe co-morbid depression or self-harmIdeally on no, or minimal, psychotropic medicationNo recent history of compulsory treatment (within the last 12 months)Good intellectual function and education—well able to comprehend the facts of the interventionPoor social and occupational function, high levels of distress—not functioning well, has poor quality of life

A ranked list of potential participants will be made in consultation with direct clinical care consultants prior to [name] approaching patient(s) one by one in rank order. If the first is not suitable or not interested, the next ranked will be approached.

## Trial Sites

The study involves collaboration between the Department of Psychiatry and the Department of Surgery at the University of Oxford. Research activities will take place at the Department of Psychiatry, University of Oxford, Warneford Hospital and the Department of Neurosurgery, John Radcliffe Hospital, Oxford.

### Phases of the Study

#### Phase I: Screening and Enrolment

Suitable patients will be identified in close liaison with specialist eating disorders clinical teams who can consult [name] initially as to their suitability. If felt to be potentially suitable, the patient will first be informed of the opportunity to take part in the study by their clinical care team. If they show interest, they will be provided with a patient information sheet (PIS) and will meet with [name] initially for a preliminary assessment. If deemed suitable, the patient will then meet [name] and [name] jointly for further information, either alone or with their family, with ample opportunity for questions. They will be given at least a week to decide whether to participate, before being consented by [name]. At all times, participants will be assured that their participation is entirely voluntary and that they may withdraw from the study at any point with no implications for their clinical care.

All patients will need to have normal electrolytes, and ECG and anaesthetic review prior to being considered fit for the operation. Patients need to have a BMI of over 13 for surgery.

#### Phase II: Pre-operative Baseline Evaluation

##### Assessment with Research Team (Repeated at All Subsequent Monthly Follow-ups)

Semi-structured interviews assessing psychiatric symptoms (including eating disorder symptoms) will be performed, along with the completion of self-report questionnaires which index eating disorder psychopathology, mood and participants’ quality of life. This is a battery of validated standardised questionnaires, of gold-standard use in studies of eating disorders and OCD, which will be used to assess mood, anxiety, obsessionality and eating disorder psychopathology:
Eating Disorder Examination (EDE) (54)Global Assessment of Functioning DSM-IV (55)Structured Clinical Interview for DSM-5 (56)Hamilton Anxiety Rating Scale (57)Hamilton Depression Response Scale (58)Yale–Brown-Obsessive Compulsive Scale and checklist (59)Yale–Brown–Cornell Eating Disorder Scale (60)EDE Questionnaire (61)Self-Starvation Scale (62)Clinical Impairment Assessment (63)WHO Quality of Life Scale (64)Beck Depression Inventory (65)State Trait Anxiety Inventory (66)Snaith–Hamilton Pleasure Scale (67)Ruminative Response Scale for Eating Disorders (68)BMI is also calculated during the baseline assessment.

##### Neuropsychological Assessment

A neuropsychological assessment battery will be carried out by a clinical neuropsychologist. This comprises the following:
WAIS-IV subtests: Vocabulary, Matrix Reasoning, Digit Span, Coding, Similarities (69)BIRT Memory and Information Processing Battery: List-Learning Task (70)Verbal Fluency (Baseline Measure of Phonemic and Semantic Fluency) (71)Rey Complex Figure task—assessment of the ability to copy, immediate recall, delayed recall (72)Iowa Gambling Task (73)Trail-Making Task Parts A & B (74)D-KEFS Colour Word Interference (75)Hospital Anxiety and Depression Scale (76).

##### Pre-operative Capacity Assessment and Ethical Sub-Study

Once each suitable patient is identified and consented, then [name], an independent psychiatrist and ethicist, will interview the patient and perform a complete MacCAT-CR assessment (77), along with an in-depth interview to explore the patient’s experience of treatment, rationale for participation and motivations for taking part in research. This follows the Oxford Neuroethics Research Paradigm which ensures a high level of capacity, voluntariness and informed consent. It is described in more detail in our recently published paper (52) and also on the registered trial online: https://clinicaltrials.gov/show/NCT01924598. We integrated this ethical sub-study from the inception of this protocol as recommended by recent consensus guidelines (78). It is guided by the foundational principles of the Nuffield Council of Bioethics report on “Intervening in the Brain” (79).

The assessment will take 2.5–3 h and can be done in sections if the patient feels tired. It will be tape-recorded and transcribed. [name] and an independent observer will separately score the MacCAT-CR. Both will also provide global assessments of capacity to consent to research. [name] will provide a detailed report of the interview and her assessment of ethical acceptability of participation for that individual. This will ensure that the needs of the research are not prioritised over those of the patient. If the patient is not suitable, the process will be repeated with the next interested and potentially suitable individual on the list.

##### Neuroimaging and Computer Tasks

Pre-operatively, patients will undergo the following:
A whole-brain MRI scan including T1, T2 and Inversion Recovery sequences at the John Radcliffe Hospital, Oxford, with a total duration of 20 min.A whole-brain MEG scan: a resting state and a food-“wanting” task (13), which will be performed at OHBA, the Warneford Hospital, Oxford, with a duration of 20 min.Computerised behavioural tasks of reward: The Leeds Oxford Food Preference Questionnaire (LOFPQ) (35), 2-step habit formation task (50) and tasks from the Cambridge Neuropsychological Test Automated Battery (CANTAB) (80).

##### True Colours

Participants will complete weekly self-report symptom questionnaires at home (estimated to be 5 min) using the “True Colours” online self-monitoring system pioneered at the University of Oxford, Department of Psychiatry, adapted for Eating Disorders by [name] by including the OxBREaD brief-rating scale: http://oxtext.psych.ox.ac.uk/true-colours. This self-report system will continue from the study entry to the study end.

#### Phase III Operative Phase: Month 2

The intervention consists of bilateral DBS targeted at the NAcc with stimulation at the ventral ALIC. The stimulation can be programmed and adjusted non-invasively by a trained clinician to minimise side effects and maximise symptom control.

The DBS system consists of three components: two electrode leads that are inserted into the brain, the implanted pulse generator (IPG) that contains a battery and a circuitry to produce the stimulus current, and the extension leads that run subcutaneously to connect these together. All three components are surgically implanted inside the body, with the IPG typically placed subcutaneously in the pectoral or the abdominal region. Patients will be implanted with the Medtronic RC pacemaker and the 3387 electrode. After implantation, the IPG can be calibrated by a trained clinician to optimise symptom suppression and control side effects. A rechargeable pacemaker lasts for 10 years and is much smaller than a non-rechargeable one, so is ideal for those who are underweight.

The whole procedure will be completed in 1 day and in total will require up to 4 days and 3 nights of inpatient stay at the John Radcliffe Hospital. On the day of surgery, the patient will be anaesthetised and the base ring fixed to the skull and a CT scan performed with a localiser fixed to the ring. The patient will then be transferred to theatre and the scalp cleansed. By fusing the structural MRI scan to the stereotactic CT scan, the trajectory to implant electrodes into the NAcc bilaterally will be calculated. Then, through bilateral scalp incisions and a twist-drill skull perforation (2.5 mm in diameter), deep-brain electrodes will be passed to target bilaterally and fixed to the skull with titanium mini plates. The scalp will then be closed, and a repeat stereotactic CT scan will be obtained to confirm electrode placement.

Having done so, back in the theatre, the electrodes will be connected to extension cables that will then be passed subcutaneously down one side of the head, behind the ear to a subcutaneous pouch below the collar bone and connected to a rechargeable pacemaker and all the wounds closed. Video recordings are used as part of the assessment process during routine implantation of DBS wires, whether taking part in a study or not, and are therefore considered part of standard operating procedure.

The day after surgery, the pacemaker will be turned on to ascertain any immediate effects of stimulation on symptoms and then switched off again. The patient will then be discharged 2 days after implantation. The stitches will be removed and the wound checked after 2 weeks. They will be assessed a month later when all wounds are healed and any acute effects of the DBS electrode insertion operation such as headaches, scalp soreness or wound tenderness have worn off. If so, DBS will be switched on: patients will be turned on to a setting of deepest contact −ve, third contact +ve, amplitude 2.5 V, pulse width 60 ms and frequency 130 Hz. Patients will have monthly assessments, and by the third visit, they will be on a final amplitude of 4 V.

#### Phase IV: Post-operative Follow-up Phase

##### Post-operative Assessments, Aiming to Track the Neural and Symptomatic Change As a Result of DBS, Will Involve

*Weekly* Self-report-rating scales of eating disorder psychopathology, anxiety and depression involving the True Colours text-messaging system started in phase I: http://oxtext.psych.ox.ac.uk/true-colours (5 min) (see Phase II: True Colours) (see Figure 1 for more details). Weekly side effects questionnaires, the SAFTEE-SI (81) and DBS side effects questionnaire (82).

Monthly

Interview with [name] and [name]. Repeat of baseline measures collected pre-operatively [see Phase II: Assessment with Research Team (Repeated at All Subsequent Monthly Follow-ups)].Joint neurosurgery–psychiatry reviews with [name] and [name], senior nurse practitioner and [name]. During this review, neurosurgical parameters (such as the degree of stimulation) and psychiatric parameters (such as experience of eating disorder and co-morbid psychiatric symptoms) will be jointly assessed. Any necessary adjustments to stimulator intensity will then be programmed.

Post-operative Neuroimaging

Resting state and food “wanting” task under MEG (13), at OHBA, at month 3 (pre-DBS switch-on), two scans in month 10 in DBS on and off conditions and at the end of study in month 15. Post-operative MRI is not possible with the stimulator implanted for safety reasons.Following each MEG scan, participants will carry out the LOFPQ food reward task. Tasks from the CANTAB (80) and a task measuring habit formation (50) will be carried out twice during the DBS on-off phase and at the end of the study (see Figure 1).

Post-operative neuropsychological assessment at 15 months (12 months after DBS switch-on) will be a repeat of those tests detailed in Section “Phase II: Neuropsychological Assessment.”

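### The two side-effect questionnaires are scheduled only after surgery, so on these forms symptoms that predate surgery cannot be told apart from effects of surgery or implantation

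*Protocol article*

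**What the plan says.** The Introduction puts safety first in aim 1: "the safety, acceptability and feasibility of DBS to the ALIC at the NAcc in SE-AN".

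Phase IV (post-operative follow-up), under the weekly measures, schedules "Weekly side effects questionnaires, the SAFTEE-SI (81) and DBS side effects questionnaire (82". This is the only mention of either questionnaire in the article.

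The pre-operative content is set out in Phase II. The research-team assessment is introduced as "Semi-structured interviews assessing psychiatric symptoms (including eating disorder symptoms) will be performed, along with the completion of self-report questionnaires" and followed by a named list of scales. The neuropsychological battery, the imaging and computer tasks, and True Colours are listed after it. Neither side-effect questionnaire is in any of these lists. Of True Colours, the other weekly measure, the article says "This self-report system will continue from the study entry to the study end".

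On timing, the Methods place the operation in month 2, "followed by the DBS switch-on at the end of month 3". Phase III (operative phase) makes switch-on depend on recovery: "They will be assessed a month later when all wounds are healed and any acute effects of the DBS electrode insertion operation" have resolved. Figure 1, captioned "Schedule of study procedures", is cited in Phase IV for further detail and is not reproduced in the text available.

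**The concern.** A side-effect inventory supports a safety statement only if each complaint can be called new, worse or already present. Patients enter with a BMI above 13 and below 16, more than seven years of illness and substantial impairment, so background complaints of the kind that a general symptom inventory records are to be expected. If the first form comes after the operation, its content mixes three things: what the patient already had, what the operation and implant caused, and acute recovery.

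Two errors are then possible. A long-standing symptom may be read as a consequence of surgery. Conversely, a real worsening may be set aside as part of the illness because its earlier level was never recorded on that form. There is no parallel control group to give a background rate. The Data Monitoring section provides for no external monitoring, so attribution rests on the study team's own records.

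**Working it through.** No stated figure needs reproducing. The check compares the instrument lists and counts forms from the stated timeline.

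**1. Which Phase IV instruments have a stated pre-operative administration?**

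| Phase IV instrument | Pre-operative counterpart in the text |
|---|---|
| True Colours (weekly) | Yes, from study entry |
| Interview and symptom scales (monthly) | Yes, Phase II research-team assessment |
| MEG, rest and food task | Yes, Phase II neuroimaging |
| Food preference, CANTAB and habit tasks | Yes, Phase II computer tasks |
| Neuropsychological battery | Yes, Phase II |
| SAFTEE-SI (weekly) | None stated |
| DBS side effects questionnaire (weekly) | None stated |

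The reading does not rest only on where one sentence sits. Phase IV itself ties True Colours, the monthly scales and the neuropsychological tests back to an earlier administration. It does not do so for the two side-effect forms.

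**2. How many forms fall in each period, per patient?**

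- Before surgery: 0 stated.
- Surgery to switch-on: the operation is in month 2 and switch-on at the end of month 3, so the interval is between about one month (operation at the end of month 2) and two months (operation at its start). That is about 4 to 8 weekly forms, assuming they begin straight after surgery; the start week is not given. Apart from a brief test the day after the operation, the stimulator is off.
- Month 10: two blinded periods of 2 weeks give about 2 forms off and 2 on. For six patients that is 6 × 2 = 12 per condition at most.

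**3. What can these forms separate?**

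For one item in one patient, let *b* be the level before surgery, *s* the shift due to surgery and implantation, and *d* the shift due to stimulation. Additivity is assumed for illustration.

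- Surgery to switch-on: expected level *b + s*
- After switch-on, stimulator on: *b + s + d*
- Month 10, stimulator off: *b + s*, if there is no carry-over

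On minus off gives (*b + s + d*) − (*b + s*) = *d*, so a stimulation effect can be examined. No period observes *b* alone. Only the sum *b + s* can be recovered, never its two parts. An item at the same level in every form is equally compatible with a long-standing symptom (*s* = 0) and with one created by the operation (*b* = 0). Pre-operative forms observe *b*, and the difference from the surgery-to-switch-on period then gives *s*.

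**The case against.** **The schedule figure is missing and the article is condensed.** This stands as a limit on confidence. When a form is first given is what such a figure would show. A reader might infer that these forms certainly start after surgery; the text supports this strongly but does not settle it.

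**Nothing says that background symptoms will be counted as effects of DBS.** This stands. A reader might infer it, but the article gives no counting or attribution rule for questionnaire items, and such rules are commonly left to the analysis plan. For serious adverse events, relatedness is judged by the Chief Investigator and not read off questionnaire scores. What can be said is that the forms cannot make the distinction.

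**Safety is not without any baseline.** This stands too. A reader might conclude that the safety aim has no pre-operative reference at all. In fact anxiety, depression, obsessionality, eating-disorder symptoms, quality of life and cognition are all measured before surgery and repeated. None of these scales is presented as a side-effect inventory, so the gap on the two forms remains.

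**There are off-stimulation references.** This stands for stimulation only. Phase III does say that switch-on waits until "any acute effects of the DBS electrode insertion operation such as headaches, scalp soreness or wound tenderness have worn off", so the last forms before switch-on should be largely clear of acute operative symptoms. They still follow the operation, as does the month-10 comparison, so neither isolates its lasting effects.

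**A short run-in catches only part of the background.** This stands in part. Assume, purely for illustration, that a symptom occurs independently in 2%, 5% or 10% of weeks. Four weekly forms would record it at least once with probability 1 − (1 − p)^4 = 8%, 19% or 34%. Infrequent symptoms would mostly be missed. Persistent symptoms, more typical of an illness lasting over seven years, would be caught far more often.

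**Little can still change.** Five of up to six patients were enrolled at publication. The article does not say how many of them had been operated on, but the change may reach few.

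**Conclusion.** The point holds in a limited form. On the text shown, SAFTEE-SI and the DBS side effects questionnaire have no pre-operative administration, so on these two instruments the pre-existing level and the effect of surgery or implantation cannot be separated. Stimulation effects can be examined, with about 4 to 8 forms before switch-on and about 2 off and 2 on in month 10 per patient.

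The size of any resulting misattribution cannot be calculated, because the article gives no symptom rates. In an exploratory study of up to six patients this is a modest weakness in safety attribution. It does not undermine the safety aim as a whole. Confidence is moderate. The conclusion assumes that the schedule figure adds no pre-operative form, and the count before switch-on assumes that the weekly forms begin soon after surgery.

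**What to change.** First check the schedule figure and the full protocol. If a pre-operative form is already there, align the text with it. Otherwise:

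- **Not yet operated on:** give SAFTEE-SI, and those items of the DBS side effects questionnaire that can be answered before implantation, weekly from study entry alongside True Colours. With surgery in month 2, this yields about four forms.
- **Classification:** class each post-operative item as new or worse against that patient's pre-operative level, or as already present.
- **Reporting:** present surgery to switch-on separately from the time after switch-on.
- **Already operated on:** flag these patients as having no side-effect baseline. Use their last forms before switch-on as the reference for stimulation effects only, not for effects of surgery.

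The cost is a few minutes a week for about four weeks, on forms already in use, with no change to treatment. The benefit is confined to patients not yet operated on. The separate reporting and the flag need no new data. Because the Discussion recommends this protocol as a model for later trials, correcting the schedule also prevents the gap from being copied.
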